#### Sample collection for SARS-Cov-2 RNA detection

Nasopharynegal swab will be used to obtain nasopharyngeal sample for the qualitative detection of SARS-Cov-2 RNA using real time PCR. Plain urine container will be used to obtain urine from participants for the detection of urine albumin and creatinine. Two collection tubes will be used for blood obtained from the ante-cubital vein: One 9-mL plain tube and another 6-mL EDTA tube. Some blood will then be dispensed into EDTA container for determination of CD4+ T cells and full blood count and viral load, while approx. 7 mls will then be dispensed into plain containers allowed to clot at room temperature, spun at 2000 g for 10 min; the serum will then be separated and cryopreserved at − 80 degree Celsius for analysis.

#### Serum biomarker analyses

Blood samples will be collected at admission (baseline), weekly, at discharge and, 4 weeks post-discharge (if possible), which is described in detail elsewhere [60] (Fig. 1). A number of plasmatic pro-inflammatory markers that play a role in endothelial dysfunction will be measured to supplement the endothelial function assessments done on the participants. Levels of serum cytokine and inflammatory markers, such as VCAM- 1, ICAM-1, TNF-α, TNF-β, and NF-κB will be measured at the same time for each participant using Luminex technology (Luminex Bio-Plex 200 system) [61, 62]. Markers of endothelial function such as ADMA will be measured using commercially available ELISA kits. Measurement of effects of COVID-19 on coagulation will be carried out via coagulation tests, calibrated automated thrombogram, thromboelastometry, impedance aggregometry, and markers of thrombin formation. These measurements are important as an increased level of D-dimer over 2500 μg/L is seen, for example, in all cases of pulmonary embolism [63]. Hence, patients with high levels of D-dimer will undergo CT angiography to visualize any accompanying thrombosis of segmental pulmonary arteries [63]. Screening for cardiovascular risk factors will be performed by measurements of (i) Lipid profile, (ii) glucose, (iii) HbA1c, (v) liver function enzymes, and (vi) high sensitivity, hs-CRP.

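### NF-κB is listed as a serum Luminex marker, but it acts inside cells, so a serum level is not a valid measure of inflammatory signalling

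*Protocol article*

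**What the plan says.** Under the heading Serum biomarker analyses, the protocol article states: "Levels of serum cytokine and inflammatory markers, such as VCAM- 1, ICAM-1, TNF-α, TNF-β, and NF-κB will be measured". The same sentence sets the platform: "TNF-α, TNF-β, and NF-κB will be measured at the same time for each participant using Luminex technology". The purpose given is general: "A number of plasmatic pro-inflammatory markers that play a role in endothelial dysfunction will be measured to supplement the endothelial function assessments". The same section refers further detail on blood sampling to a cited source, "which is described in detail elsewhere [60"].

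The specimens are described under Sample collection for SARS-Cov-2 RNA detection. Blood for the plain containers is left to clot and is centrifuged, and "the serum will then be separated and cryopreserved at − 80 degree Celsius for analysis". The cell-containing blood has a different use: "Some blood will then be dispensed into EDTA container for determination of CD4+ T cells and full blood count and viral load". The article mentions no cell isolation, lysate or nuclear extract, and no assay of phosphorylation or DNA binding.

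**The concern.** The named analyte does not fit the named specimen. VCAM-1, ICAM-1, TNF-α and TNF-β have forms that are shed or secreted into the circulation, so a serum panel suits them. NF-κB does its work inside the cell: it is released from its inhibitor, is phosphorylated, moves to the nucleus and binds DNA. Preparing serum removes the compartment in which those changes occur.

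What is at stake is interpretation. The Background section says that the project will examine how far inflammation induced by COVID-19 contributes to changes in endothelial function and coagulation, and it describes alveolar and endothelial damage in severe disease. If part of a serum NF-κB value comes from protein leaking out of damaged cells, the value could vary with severity. A difference between the three groups, or over time, could then be read as inflammatory signalling when it does not show that. More participants would not help, because the problem is what the assay measures and not how precisely it does so. The confounders named in the statistical section (age, gender, ethnicity, smoking, alcohol consumption, medication and BMI) include nothing that stands for cell damage or haemolysis, although that list is given as examples.

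**Working it through.** No arithmetic applies. The article gives no figure on this point, and the conclusion depends on no numerical design input. The check sets the statements on analyte, assay and specimen side by side.

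1. **Analyte.** Five markers are named: VCAM-1, ICAM-1, TNF-α, TNF-β and NF-κB. The list is open, since the markers are introduced as examples, so the full size of the panel is unknown.
2. **Matrix stated for the analyte.** The section heading and the sentence itself both say serum. The preceding sentence speaks of plasma markers. That inconsistency does not change the result, because serum and plasma are both the fluid left after the cells have been separated off.
3. **Assay.** One multiplex platform reads all the markers together for each participant. NF-κB is therefore planned in the same run, on the same specimen, as the shed and secreted proteins.
4. **Specimen handling.** The blood is clotted and spun at 2000 g for 10 min, and the serum is then frozen. The uses stated for the EDTA blood are the CD4+ count, the full blood count and the viral load. No stated use would supply a cell preparation for NF-κB.
5. **Fit.** For four of the five named markers, the specimen contains the form to be measured. For NF-κB, the informative state is intracellular, and the described specimen is cell-free. A measured concentration could at most represent protein that has left its cells.
6. **Reach.** None of the objectives under Aim and objectives names NF-κB. The sample size rests on an HIV prevalence of 4.9% and on comparison with the EndoAfrica study, not on any biomarker. The Background section assigns the evaluation of endothelial function to FMD and ADMA. The mismatch therefore stays within one supplementary marker.

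**The case against.** The strongest reply is that the article's account of specimens is incomplete. The sample-collection section is headed for SARS-CoV-2 RNA detection. It lists no tube or handling for the coagulation work planned elsewhere, such as thromboelastometry and impedance aggregometry, which cannot be run on clotted serum. It does not say what becomes of the cells. Further sampling detail is referred to a source that is not shown. Silence about a cell-based step is thus weak evidence that none exists. This stands, and it rules out any claim that serum is the only material kept for biomarkers or that the cells are discarded. It does not remove the point. The article does not leave the matrix open: it states serum, so an unseen cell-based step would contradict the printed text, which would still need correction.

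A second reply is that the article nowhere says it will measure NF-κB activation. It speaks only of pro-inflammatory markers with a role in endothelial dysfunction. This is also correct, and an intention to report activation should not be attributed to the investigators. Even so, the stated purpose needs a marker that carries information about inflammation, and a serum NF-κB level does not validly supply it.

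A reader might infer more than this: that the value will lie near or below the detection limit, that any signal is simply cell lysis, or that a fifth of the panel is lost. The documents support none of these. They give no assay performance data, release from damaged cells is a possible contribution and not an established explanation, and an open list gives no denominator for a percentage.

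**Conclusion.** The point holds as a minor one. As written, the article plans NF-κB as a serum marker, and a serum level of an intracellular transcription factor is not a valid measure of inflammatory signalling, even if the assay returns a number. Any contribution from damaged cells could differ with disease severity, but its size cannot be stated from the documents.

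The conclusion rests on two things: the article's own statement that the marker is read in serum, and the textbook fact that NF-κB acts inside cells. It would change if the sources not shown specify a cell-based specimen and assay. The defect would then be one of description and not of measurement. The stronger reading, that this undermines the study's endothelial or inflammatory findings as a whole, is not supported. FMD, IMT, pulse wave velocity, the retinal measures, ADMA, the other named markers and the sample size are unaffected.

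**What to change.** Remove NF-κB from the list under Serum biomarker analyses, and draw no conclusion about NF-κB signalling from serum. If a cell-based specimen and assay is already planned in the full protocol or laboratory documents, correct that section instead so that it names the specimen and the method for this marker. A soluble downstream marker read on the same serum could be added if such a read-out is wanted, but this is optional.

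Deletion costs nothing and changes neither blood collection nor the visit schedule. The downside is that the study would have no NF-κB read-out. An optional substitute would be a choice of kit on serum already collected.

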#### Data collection, management and statistical analysis

Data from the questionnaires, clinical evaluations, and biochemical analyses will be gathered and managed by Research Electronic Data Capture (REDCap) tools hosted at the Walter Sisulu University [64] (Fig. 1).

Statistical analyses will be performed in collaboration with the Biostatistics Unit in the Centre for Evidence-based Health Care, Walter Sisulu University. Descriptive statistical models (ANOVA, Chi Square) will be used for inter-group comparisons, and associations between independent and dependent variables will be tested by multivariate regression analysis models, taking into account confounding variables such as age, gender, ethnicity, smoking, alcohol consumption, medication, and BMI. For long term changes in the same individual, a repeated measures model approach will be engaged.

Strijdom et al., in their discussion of the *EndoAfrica* study design, suggested that sample sizes of up to 300 participants are sufficient to secure statistical power [39]. Fischer’s formula was also used for calculation of sample size: (n) = Z2P (1-P)D2. Since there are no data on the number of people with coinfection of HIV and SARS-CoV-2, the sample size was calculated using the prevalence rate of PLHIV of 4.9% in SSA (UNAIDS report, 2019) [65]. To achieve statistical significance, 94 HIV-infected persons are required. Since we have 3 groups, we will require a total of (94 × 3) = 282 participants. Due to 20–30% drop out rate, 20 more persons in each group will be added to this number, so that the final number of participants required in this project has similar participant numbers that were recruited in the *EndoAfrica* study (282 + 60 = 342 at each recruiting center). Demographic and background data (e.g., smoking and drinking status, BMI) will also be collected and included in the linear regression models as putative confounders [66].

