**Methods:**

A total of 1026 patients will be included into this study. Cardiovascular research PLHIV with (*n* = 114 in each of the three recruiting centers) - or without - ART (*n* = 114 in each of the three recruiting centers) with COVID-19 and HIV-negative with COVID-19 (*n* = 114 in each of the three recruiting centers) will be carried out via clinical and biochemical measurements for cardiovascular risk factors and biomarkers of cardiovascular disease (CVD). Vascular and endothelial function will be measured by brachial artery flow-mediated dilatation (FMD), carotid intima-media thickness (IMT) assessments, and retinal blood vessel analyses, along with vascular endothelial biomarkers and cogualation markers. The correlation between HIV-infection in COVID-19 PLHIV with or without ART and its role in enhancement of cardiovascular risk and endothelial dysfunction will be assessed at admission, weekly, at discharge and, 4 weeks post-discharge (if possible).

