**Fig. 1 Fig1:**
[figure not shown]
Project aims and objective established for the ENDOCOVID project. Shown are also the partner institutions and the impacts of the project

Three groups of participants will take part in this project:
PLHIV without ART but with COVID-19 (*n* = 114 in each recruiting center)PLHIV with ART and COVID-19 (*n* = 114 in each recruiting center)HIV-negative patients with COVID-19, sex−/age-matched (*n* = 114 in each recruiting center)

The following objectives will be investigated (Fig. 1):
Prevelance of PLHIV among those admitted for COVID-19 to clinics in South Africa and Nigeria.Assessment of the incidence of acute respiratory distress syndrome, admission to ICU, fatal course of disease (30-days mortality), and thromboembolic events in hospitalized patients included in the study.Evaluation of the influence of ART on severity of COVID-19 in PLHIV (with or without ART) as well as clinical presentation, changes of endothelial/vascular function and biomarkers.Evaluation of the effects of COVID-19 on endothelial/vascular function and thrombotic factors over infection and after recovery.Correlation of hospitalization and mortality of COVID-19 infected PLHIV (with or without ART) and HIV negatives with co-morbidity incidence;Assessment of the incidence of obesity and insulin resistance in the 3 groups.

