### Possible limitations

Although the ENDOCOVID project will provide us a lot of new information, it is associated with several risks for which have been proposed impact alleviation strategies. These risks include:
All HIV-infected patients in South Africa must immediately begin with ART and it may limit our ability to recruit ART naïve participants. All of these untreated HIV-infected participants will serve as their own untreated controls during the cycle of our project, and we will be able to observe endothelial changes after initiation of ART.Lack of patients because of current lockdown and low prevalence of COVID-19 in SSA region. This may require that we have to expand our cohorts to more regions. That is why we have included two partners from SSA: South Africa and Nigeria. It has also been seen in most parts of the world that the period following the lockdown is accompanied by an increase in the number of COVID-19 related infections. So, between the two countries, we should have no problem in recruiting the requied number of participants to reach statistical significance for this study.The severity of the disease can limit our collection of samples and data about the patient, especially in those cases where the patients with COVID-19 are in the intensive care units and difficult to access for research purposes. However, we will work with clinicians to ensure that we can also evaluate the patients during acute care. Furthermore, patients at home and discharged from the hospital will also be recruited and their data collected. The complete data collection will be done by motivated healthcare partners of this project.It is possible that at the end of the project, we could be confronted with missing data. As missing data can limit the statistical comparisons across groups, we will reduce this via close collaborations with hospital personnel. In addition, we will take the required measures in the statistical analysis plan to deal with missing data.A possible limitation of this project is that it may not always be possible to collect post discharge data at 4 weeks. This may arise due to issues with patitence compliance and/or lockdowns. Every patient will be advised to report back 4 weeks post-discharge for a follow up assessment. Unpredictable and unplanned lock-downs, however, could make post-discharge data collection difficult.Another obvious limitation related to FMD and IMT measurements is the fact that these measurements are operator dependent and how inter-operator variability. It is also important that same vascular regions are measured in each participant at the 4–6 weeks’ follow-up visit. These risks will be reduced by limiting the number of operators in the research team, and training them intensively, and ensuring strict quality control steps by independent experts in this field.As the ART regimens differs across the recruitment sites, and different types of ART may have different effects, it could potentially influence the data that will be collected across the two SSA countries. When analyzing and interpreting the data from the different sites, details of the ART regimes will also be taken into account.

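### Centre is not named in any planned group comparison, although recruitment is by quota per centre and the protocol itself describes site-related risks

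*Protocol article*

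**What the plan says.** Recruitment is fixed by centre. The abstract states that "A total of 1026 patients will be included into this study", and the sample size paragraph arrives at "282 + 60 = 342 at each recruiting center". The Aim and objectives section gives the same quota of 114 per centre to each of the three groups. Study design lists ethics approvals from one South African and two Nigerian institutions.

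The section on data collection, management and statistical analysis names ANOVA and chi-square for comparisons between groups, with no adjustment mentioned. It then names multivariable regression "taking into account confounding variables such as age, gender, ethnicity, smoking, alcohol consumption, medication, and BMI". A later sentence adds that background data ("e.g., smoking and drinking status, BMI) will also be collected and included in the linear regression models as putative confounders"). For change within a person, "a repeated measures model approach will be engaged". Centre, site, country and operator appear in none of these statements.

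Possible limitations raises three matters that vary by centre or country:
- On FMD and IMT, "these measurements are operator dependent". The remedies offered are few operators, intensive training and independent quality control.
- "All HIV-infected patients in South Africa must immediately begin with ART and it may limit our ability to recruit ART" (the sentence goes on to the treatment-naïve group).
- ART regimens differ between sites and could influence the data; regimen details are to be considered in analysis and interpretation.

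**The concern.** One objective is the influence of ART on COVID-19 severity, endothelial and vascular function and biomarkers. It rests largely on comparing ART-naïve with ART-treated patients. A comparison pooled over centres is protected from centre differences only while each group draws the same share of its patients from each centre. The equal quotas achieve this if they are filled. The protocol itself names a reason why one cell of the group-by-centre table, South African ART-naïve patients, may not fill.

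If that happens, the ART-naïve group contains fewer South African patients than the groups it is compared with. Any difference between centres in measurement, local care or case mix then appears partly as an effect of ART. Fewer operators and better training may shrink that difference, but nothing named in the analysis removes it.

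**Working it through.** **Inputs from the protocol.** Three groups, three centres, 114 per cell. The planned totals reproduce: 94 + 20 = 114; 3 × 114 = 342 per centre (also 342 per group over the three centres); 3 × 342 = 1026. How the 94 was obtained does not matter for this point.

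**Assumptions, not in the protocol.** One of the three centres is South African (inferred from the ethics approvals). All cells other than South African ART-naïve are filled. The South African centre differs from the Nigerian centres, taken as alike, by d within-centre SD in the mean outcome. Tests are two-sided at 5%. The protocol gives no centre effect, SD or expected shortfall.

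**Case 1: all quotas filled.** Each centre supplies 114/342 = 1/3 of every group, so the centre difference cancels and the bias is 0. If centre explains a fraction R² of outcome variance, leaving it out multiplies the residual variance by 1/(1 − R²):
- R² = 5%: 1/0.95 = 1.05
- R² = 15%: 1/0.85 = 1.18

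The standard error grows by the square root, about 3% to 8%.

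**Case 2: South African ART-naïve quota short.** With n recruited there, the centre supplies n/(n + 228) of the ART-naïve group and 1/3 of each comparison group. The share of d that enters the unadjusted contrast is 1/3 − n/(n + 228).

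- n = 20: 20/248 = 0.081; 0.333 − 0.081 = 0.253
- n = 0: 0.333 − 0 = 0.333

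The table gives the resulting bias and type I error for a true ART difference of zero. The false-positive rate uses a normal approximation: the unadjusted standard error includes the centre spread, while the true sampling error given the centre counts is √(1/(n + 228) + 1/342).

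| South African ART-naïve recruited | Share of d entering | Bias in SD, d = 0.2 / 0.5 / 0.8 | Type I error, d = 0.2 / 0.5 / 0.8 |
|---|---|---|---|
| 114 | 0 | 0 / 0 / 0 | 4.9% / 4.4% / 3.6% |
| 57 | 13% | 0.03 / 0.07 / 0.11 | 6% / 12% / 23% |
| 20 | 25% | 0.05 / 0.13 / 0.20 | 9% / 32% / 65% |
| 0 | 33% | 0.07 / 0.17 / 0.27 | 12% / 49% / 87% |

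The direction of the bias is unknown, because the sign of d is unknown.

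**With centre in the model.** Under an additive centre effect the bias is 0 in every row. For a comparison of two groups, the adjusted standard error is 1/√Σ[nₖ × 114/(nₖ + 114)], summed over centres k, where nₖ is the ART-naïve count in centre k.
- All quotas filled: Σ = 3 × 57 = 171, SE = 0.0765 SD, against 0.0768–0.0817 unadjusted for d = 0.2–0.8.
- n = 20: Σ = 17.0 + 57 + 57 = 131.0, SE = 0.087 SD, against 0.084–0.087 unadjusted.
- n = 0: Σ = 114, SE = 0.094 SD, against 0.086–0.088 unadjusted. The South African centre then adds nothing directly to the contrast.

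**The case against.** **The lists are open, and an analysis plan is not shown.** Both covariate lists are introduced as examples, and the limitations section mentions a statistical analysis plan. A reader might infer that centre has been excluded from the models. The text does not support that; it shows only that centre is not named. What remains is that the article does state its methods and seven covariates, and describes site-related risks without carrying them into the analysis.

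**Quotas already balance centre.** Correct while they are filled; there is then no confounding at all. The protection fails only with uneven filling.

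**The shortfall is not a forecast.** A reader might infer that ART status will be tied to country. The protocol says only that the rule may limit recruitment, and it does not describe Nigerian practice. The figure of 20 of 114 is illustrative.

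**Operators may not be nested in centres.** The protocol does not say that they are. It is plausible across two countries, but it is an assumption.

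**Other adjustment helps.** Ethnicity, if recorded in detail, could absorb much of a difference between countries, and medication some of it, so the shares above are upper figures for the adjusted regression. Ethnicity does not measure operators or local care. Regimen is undefined for HIV-negative patients and for ART-naïve patients at baseline.

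**Within-person change is safe.** The protocol treats untreated patients as their own controls. A stable centre shift cancels from change within a person, so the concern is confined to between-group comparisons of level.

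**Conclusion.** The point stands as a low-cost improvement to the stated analysis, not as an error that invalidates it. With all quotas filled, the loss is precision only: residual variance about 5–18% larger for an assumed 5–15% of variance due to centre. With a shortfall confined to South African ART-naïve patients, 25% (20 of 114 recruited) to 33% (none recruited) of any centre difference enters the unadjusted cross-sectional ART contrast.

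Whether this matters in practice depends on two quantities that the protocol does not give: the size of the centre difference and the size of the shortfall. At 0.2 SD and half the quota filled, the effect is slight (type I error 6%). At 0.5 SD and no such patients, it is serious (49%). The documents do not support saying that bias will occur, only that the named analyses would not guard against it.

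**What to change.** 1. Name centre as a fixed effect in the between-group regression models and in the repeated-measures model.
2. Base the group comparisons on these models rather than on unadjusted ANOVA and chi-square: group plus centre for continuous outcomes, and a logistic model with centre for yes/no outcomes. Unadjusted tables can stay as description.
3. Report the group contrasts by centre as a consistency check, wherever all compared groups are present in that centre.
4. State that if a centre recruits no ART-naïve patients, its own ART-naïve contrast cannot be estimated, and the pooled contrast rests on the other centres and on an additive centre effect.

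The cost is two parameters with three centres, plus one for each further centre if the cohort is extended to more regions, as the limitations section allows. Centre is known for every patient, so no new data are needed and the planned 1026 does not change. If the ART-naïve cell in one centre is empty, the adjusted standard error is larger than the unadjusted one (about 0.094 against 0.086–0.088 SD for two groups), which reflects how little that centre can say about the contrast.

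### The 94 per group comes from a precision formula for one prevalence, so it cannot support the claim of statistical significance between three groups; the added 20 per group also falls short of the stated dropout

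*Protocol article*

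**What the plan says.** The sample size is set out under *Data collection, management and statistical analysis*. It gives two supports.

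- The design discussion of the earlier EndoAfrica study, which is said to have "suggested that sample sizes of up to 300 participants are sufficient to secure statistical power".
- A formula: "formula was also used for calculation of sample size: (n) = Z2P (1-P)D2". The superscripts and the division sign were lost in text extraction; this is Z²P(1−P)/D². For its input, "the sample size was calculated using the prevalence rate of PLHIV of 4.9% in SSA".

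The text then concludes: "To achieve statistical significance, 94 HIV-infected persons are required". It continues: "Since we have 3 groups, we will require a total of (94 × 3) = 282 participants". For losses: "Due to 20–30% drop out rate, 20 more persons in each group will be added to this number", which leads to "282 + 60 = 342 at each recruiting center". The Abstract gives 114 per group in each of three centres and 1026 in all.

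The same section plans ANOVA and chi-square tests between groups, multivariable regression, and a repeated-measures model. *Possible limitations* repeats the significance claim: "we should have no problem in recruiting the requied number of participants to reach statistical significance for this study".

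**The concern.** A formula that fixes the width of a confidence interval for one prevalence is used to claim that a number per group secures significance between groups. These are different questions. The first needs a prevalence and a margin. The second needs an endpoint, a difference, its variability and a power.

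If the claim stands, a reader will take the study as sized to find group differences, although nothing in the article says how large a difference. A null result could then not be interpreted, because the difference it makes unlikely is not known. Nor does the article say whether groups are to be compared within a centre or across all three, and the detectable difference depends strongly on that.

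**Working it through.** **Inputs from the article:** P = 0.049; 94 per group before dropout; 20 added, giving 114 per group per centre; three centres; dropout 20–30%. **Not stated:** Z, D, power, effect size, SD, endpoint.

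**1. The stated 94.** n = Z²P(1−P)/D², with P(1−P) = 0.049 × 0.951 = 0.0466. Z = 1.96 is assumed, so Z²P(1−P) = 0.1790.

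| D (assumed) | n |
|---|---|
| 5 points | 71.6, so 72 |
| 4.5 points | 88.4, so 89 |
| 4 points | 111.9, so 112 |

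At D = 5 points, 90% confidence gives 51, Z = 2 gives 75 and 99% confidence gives 124. Solving back for 94 at Z = 1.96: D = √(0.1790/94) = 0.0436, about 4.4 points. So 94 is not reproduced under the usual choices tried, but with Z and D unstated it cannot be called miscalculated either.

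**2. What the formula's n means.** It is the number of people to survey so that one prevalence is estimated to within ±D. Among 94 people at 4.9%, 94 × 0.049 = 4.6, about 5, would be HIV-infected. The article reads the same 94 as HIV-infected persons and then as the size of each of three groups, one of which is HIV-negative. Since the groups are formed by HIV and ART status, HIV prevalence is not an outcome in any of them. Multiplying by three does not turn the result into a sample size for a comparison. This step does not depend on Z or D.

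**3. The dropout allowance.** 20/114 = 17.5%. To keep 94 per group, one would need 94/0.80 = 117.5, so 118, at 20% loss and 94/0.70 = 134.3, so 135, at 30%. At those losses 114 leaves 91.2 and 79.8. The 20 looks sufficient only as a share of the 94 (20/94 = 21.3%), and even then only at the lower end of the range.

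**4. What the planned numbers deliver.** Pooled, each group has 3 × 114 = 342. (This is also the total per centre, 3 × 114.) After 20–30% loss: 342 × 0.80 = 273.6 and 342 × 0.70 = 239.4, so 273 to 239 evaluable. The smallest detectable pairwise difference in SD units, for two equal groups without adjustment, is (z₁₋α/₂ + z₀.₈₀) × √(2/n). The multiplier is 1.960 + 0.842 = 2.802 at two-sided 5%, and 3.236 with Bonferroni for three pairs.

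| Evaluable per group | 80% power, two-sided 5% | Bonferroni, three pairs |
|---|---|---|
| Pooled, 273 (20% loss) | 0.240 SD | 0.277 SD |
| Pooled, 239 (30% loss) | 0.256 SD | 0.296 SD |
| One centre, 91 (20% loss) | 0.415 SD | 0.480 SD |
| One centre, 80 (30% loss) | 0.443 SD | 0.512 SD |

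With no loss, 342 per group detects 0.214 SD and 114 detects 0.371 SD.

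**The case against.** Four points can be made for the article.

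- **Z and D may be in the full protocol.** The article condenses it, and leaving them out is no fault in itself. This stands. A reader might infer that 94 is an arithmetic error for 72. The document does not support that: 72 rests on an assumed Z and D, and D of about 4.4 points gives 94. The misuse of the formula, however, is stated in the article and no value of Z or D cures it.
- **The formula is not the only basis.** The article cites the earlier study first and aims at similar numbers. That source is not at hand, so its adequacy cannot be judged either way. As cited, it gives no endpoint, effect or power, and a figure of up to 300 participants does not produce 94 per group.
- **The total may be ample.** This also stands. A reader might infer that the study is too small, but pooled it detects fairly small differences. The defect is that the stated derivation does not show this.
- **The group comparisons are labelled descriptive.** That label does not fit with a sample size said twice to reach statistical significance.

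A reader might also note that 72 × 1.3 = 93.6 and infer that 94 already contains a 30% dropout allowance, which would then be added twice. Nothing in the text says so. The article introduces dropout only after the 94, and the match itself rests on the assumed 72.

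**Conclusion.** The concern holds as a wrong justification, not as a wrong total. The significance claim attached to 94 per group has no basis in the calculation given, for any Z and D. Separately, the added 20 per group cover 17.5% loss, below the whole of the article's own 20–30% range.

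After that loss, the pooled design has about 239–273 evaluable per group and detects about 0.26–0.24 SD pairwise at 80% power and two-sided 5%, or about 0.30–0.28 SD with Bonferroni for three pairs. One centre alone, with about 80–91 per group, detects about 0.44–0.42 SD.

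These figures assume equal groups, a continuous endpoint, no covariate adjustment and no allowance for differences between centres. The article itself warns that ART-naïve participants may be hard to recruit, and a smaller group would raise the detectable difference in its comparisons. Comparisons at admission would lose fewer participants than those at follow-up. Power of 80%, two-sided 5% and Bonferroni are conventions chosen here; the article names none of them.

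**What to change.** Keep 1026 and change the wording.

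1. Remove the statements about achieving or reaching statistical significance in *Data collection, management and statistical analysis* and in *Possible limitations*, and remove the prevalence formula as the basis for group size.
2. State that group comparisons pool the three centres.
3. State what the planned numbers deliver after the article's own dropout. For example: with 342 enrolled per group and 20–30% loss, about 239–273 are evaluable per group, giving 80% power at two-sided 5% for a pairwise difference of about 0.26–0.24 SD (about 0.30–0.28 SD with Bonferroni for three pairs), if groups are equal. The sponsor should name the endpoint to which this applies; the article does not single one out.
4. Correct the dropout sentence: 20 per group allow for 17.5% loss.
5. If the formula is kept for the objective on the prevalence of PLHIV among COVID-19 admissions, state Z and D and apply it to the number of admissions screened, not to group size.

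The cost is protocol wording only, with no added patients or measurements.
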